##### Aim 2: Personal Network Study

We will use quantitative personal network analysis to address Aims 2a, b, and c. Personal network measures consist of compositional variables, which describe who is in the network, and structural variables, which measure how network alters are arranged around the ego. Personal network measures will be obtained at two points, baseline and 12-month follow-up. Compositional variables for each alter include: demographic data (ie, sex and age); relationship to participant (ie, relationship, how close, frequency of interaction, and smoking- and quitting-related support); and smoking-related information (ie, use of tobacco products, previous and current smoking status, and quit attempts). Structural variables will be calculated in R package *egor* based on alter pairs that very likely interact and include: density (ie, the extent to which all possible connections between alters are present), alter centrality measures (ie, to identify the most central individuals in the network), network centralization (ie, the extent to which a network is dominated by one or a few alters), and measures of subgroups (ie, to identify cohesive or disconnected subgroups). Additionally, some combined compositional and structural variables will be calculated with smoking status and alter centrality measures.

Descriptive statistics will be run on all compositional and structural personal network variables at both time points. We will assess using analysis of variance differences in network measures between the Helpers Stay Quit (vs usual care completers, completers who carried out helping conversations (vs no helping conversations), and completers who relapsed (vs abstained). Paired samples *t* tests will be used to compare network measures between the two different points.

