##### Aim 3: Mediational Analysis

Using data from Aims 1 and 2, we will use multiple mediation models to investigate mechanisms of Helpers Stay Quit. Specifically, we will estimate the direct effects of the intervention on abstinence, as well as the indirect effects that are mediated through the personal networks of participants and longitudinal change in scores collected through surveys. Potential candidates for mediation include the number of helping conversations, change in personal network variables (smoking status, smoking status and degree centrality, smoking status and sex, density, and degree centralization), and change in patient-reported outcome variables from the cognitive and emotional measures. To narrow down the list of potential mediators from the conceptual framework, we will first examine relationships between the intervention arm and the mediator, as well as the mediator and the outcome variable. Variables associated with both the intervention and abstinence, with a *P* value of .1, will be included in this analysis as potential mediators. Variables associated with abstinence but not treatment arm at the 0.1 alpha level will be included as a covariate but not explored further as a mediator. For those who meet the initial criteria for a mediator (associated with both intervention arm and outcome), we will examine direct and indirect effects using causal mediation modeling [80].

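### Aim 3 screens change-score mediators against abstinence without naming their baseline value, which can understate the mediator-to-abstinence path and drop a true mediator

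*Protocol article*

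**What the plan says.** The Aim 3 section (Mediational Analysis) seeks indirect effects "mediated through the personal networks of participants and longitudinal change in scores collected through surveys". One candidate mediator is a count, that of helping conversations. The network candidates are given as "change in personal network variables (smoking status, smoking status and degree centrality, smoking status and sex, density, and degree centralization"). The survey candidates are given as "change in patient-reported outcome variables from the cognitive and emotional measures". Selection comes before modelling: "we will first examine relationships between the intervention arm and the mediator, as well as the mediator and the outcome variable". The threshold is then set: "Variables associated with both the intervention and abstinence, with a *P* value of .1, will be included in this analysis as potential mediators". Only candidates that pass both sides go on to causal mediation modelling.

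No formula for change is given. A mediator's baseline value is neither included nor excluded, in the screen or in the models. The values exist: the Aim 2 section states "Personal network measures will be obtained at two points, baseline and 12-month follow-up", and Table 1 shows every survey scale in the Cognitive or Emotional Measures section collected at baseline.

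Two covariate rules could bear on the point. General Quantitative Approaches admits participant-level covariates related to the outcome at P<.2 into multivariate analysis. Aim 3 adds: "Variables associated with abstinence but not treatment arm at the 0.1 alpha level will be included as a covariate". Neither is said to apply to the screen.

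**The concern.** Arm is randomised, so the arm-to-mediator comparison is unbiased whether the mediator is a change or a follow-up value. The mediator-to-abstinence relation is observational. A change score has the baseline value subtracted inside it, so anyone who starts high tends to show less change. If abstinence depends on the level reached, or on the starting level as well, the slope on change alone is not the mediator's effect.

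Level effects are plausible here. The Introduction describes smokers in the network as a source of cues and of cigarettes, and that exposure depends on how many smokers are present, not only on how the number has moved. At stake is Aim 3, a numbered specific aim: indirect effects could be understated, and a real mechanism could be discarded at the screen, where no later adjustment can bring it back.

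**Working it through.** **Inputs from the article (Power and Sample Size).** N = 940, control rate 0.25, difference 10 points, 30% dropout, χ² test without continuity correction, and d = 0.26 for continuous measures. Two-sided alpha 0.05 is assumed.

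**The plan's own figure first.** n per arm = [1.96·√(2·0.30·0.70) + 0.8416·√(0.25·0.75 + 0.35·0.65)]² / 0.10² = (1.270 + 0.542)² / 0.01 ≈ 329. The total is 658, and 658/0.7 = 940, as stated; power at 329 per arm is 0.801. At 329 per arm, d = 0.26 has power 0.915, against 90% stated. The article gives no figure for the mediation analysis, so 658 completers and an arm effect of 0.26 SD are carried forward as assumptions.

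**Algebra.** Let M0 and M1 be the baseline and follow-up values, D = M1 − M0, and let the log-odds of abstinence contain b·M1 + c·M0. Let the baseline SD be 1, the follow-up SD k and the correlation ρ. In the linear approximation, the slope on D alone is

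[b(k² − ρk) + c(ρk − 1)] / (k² + 1 − 2ρk).

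With k = 1 this is (1 − ρ)(b − c) / [2(1 − ρ)] = (b − c)/2 at any ρ. As a fraction of b:

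- k = 1: 0.50 for c = 0; 0.25 for c = b/2; 0.75 for c = −b/2; 1.00 for c = −b (change itself drives abstinence).
- c = 0, ρ from 0.3 to 0.8: 0.34 down to 0.00 at k = 0.8; 0.66 to 1.00 at k = 1.25; 0.77 to 1.24 at k = 1.5.

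With M0 in the model, b·M1 + c·M0 = b·D + (b + c)·M0, so the coefficient on D is b in every case.

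**Simulation.** Logistic outcome with intercept −0.9, 658 completers, 800 runs per setting, screens at P<.1. Coefficients come from models that also contain arm. Each pair is change alone / baseline added.

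| Setting | Mediator coefficient | Passes both screens |
|---|---|---|
| b=0.3, c=0, ρ=0.5, k=1 | 0.15 / 0.31 | 0.54 / 0.92 |
| b=0.3, c=0, ρ=0.7, k=1 | 0.15 / 0.30 | 0.44 / 0.83 |
| b=0.2, c=0, ρ=0.7, k=1 | 0.10 / 0.21 | 0.26 / 0.54 |
| b=0.5, c=0, ρ=0.5, k=1 | 0.24 / 0.50 | 0.86 / 0.99 |
| b=0.3, c=0.15, ρ=0.5, k=1 | 0.08 / 0.31 | 0.22 / 0.92 |
| b=0.3, c=−0.15, ρ=0.5, k=1 | 0.23 / 0.31 | 0.83 / 0.91 |
| b=0.3, c=−0.3, ρ=0.5, k=1 | 0.30 / 0.30 | 0.92 / 0.90 |
| b=0.2, c=0, ρ=0.5, k=1.5 | 0.17 / 0.20 | 0.84 / 0.90 |
| b=0.2, c=0, ρ=0.7, k=1.5 | 0.20 / 0.20 | 0.79 / 0.77 |

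**Arm-to-mediator path.** With k = 1, the standard error with change alone exceeds the baseline-adjusted one by the factor √[2/(1 + ρ)]: 1.15 at ρ = 0.5 and 1.08 at ρ = 0.7. The arm-side screen is passed in 0.95 against 0.98 of runs at ρ = 0.5. This is a small loss of precision and no bias.

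**Would the covariate rules bring baseline in?** With c = 0 and k = 1, M0 met P<.2 against the outcome in 43% to 100% of runs, depending on b and ρ. In those settings, adjustment in the final model would depend partly on chance. The rules also come too late for a candidate already removed by the screen.

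**The case against.** The strongest reply is that the fault is read into silence. A reader might infer that the plan commits to raw, unadjusted differences. The text does not say so: it gives no formula, it speaks of "longitudinal change in scores collected through surveys", and the Aim 1 section analyses change in the same scales with mixed models. Model equations are commonly left to an analysis plan. This stands, and the point is therefore put as an unstated adjustment, not as a declared omission. It does not remove the point, because the form of the mediators and the two-sided screen are stated choices, and the article says results will follow the plans it describes.

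Second, the covariate rules may restore baseline in the final model, most reliably where the bias is worst: at b = 0.4 with a same-direction baseline effect, baseline met P<.2 in every run of a further simulation. That also stands for the final model. It does not help at the screen.

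Third, change is the construct in the article's own theory: cessation fatigue is framed as declines, and benefit is expected from having fewer smokers in the network. If change does drive abstinence, change alone is right. The baseline-adjusted model gives the same coefficient in that case (0.30 against 0.30), with a pass rate of 0.90 against 0.92, so little is lost by adjusting.

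**Conclusion.** The concern holds in limited form. As written, the Aim 3 screen can understate the mediator-to-abstinence path and discard a true mediator. If only the follow-up level matters and the SDs are equal, the coefficient is halved; with b = 0.3 and ρ = 0.5 the chance of passing both screens falls from about 0.92 to 0.54. A baseline effect in the same direction makes it worse (0.22 with c = 0.15).

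A reader might infer that the path is always cut by half or more. The document does not support that. It gives no SDs, correlations or mediator effects, and the result needs a zero or same-direction baseline effect and a follow-up SD no larger than the baseline SD. All participants are abstinent at baseline, so a wider spread at follow-up is plausible. The loss is then smaller, nil or even reversed, and it is nil when change drives abstinence.

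The helping-conversation count is not a change score and is unaffected. The arm-to-mediator path is unbiased, and the primary outcome is not touched. This is a low-cost improvement to Aim 3, not a flaw in the trial.

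**What to change.** In the Aim 3 section, state that each network and patient-reported mediator's own baseline value is a covariate in three places: the P = .1 screen (on both sides), the mediator model and the outcome model. The mediators need not be redefined: once baseline is in the model, change and the follow-up value give the same mediator coefficient.

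The cost is one sentence of analysis wording. Baseline values are already collected under Table 1, and no new data are needed. Where change alone would have been adequate, the chance of passing both screens drops by about 2 points (0.92 to 0.90 and 0.79 to 0.77 in the settings above). Twelve-month follow-up was still incomplete when the article was submitted, so the wording can be fixed before the mediation analysis is run.

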#### Cognitive or Emotional Measures

A dynamic model of smoking relapse is the organizing framework guiding the overall intervention and evaluation approach [14]. Selected measures evaluate possible factors in “cessation fatigue,” a latent construct proposed to contribute to “relapse proneness” and operationalized by declines in motivation, expectancy for success, coping attempts, self-efficacy, and self-control resources [14]. To explore the concept of “cessation fatigue” [16], the following patient-reported outcome measures are collected at baseline, 3, 6, 9, and 12 months post study enrollment: cessation fatigue [17], Abstinence Related Motivational Engagement – Short Form [40], smoker versus quitter identity [41], smoker group identity [41], residual attraction and vulnerability to smoking [42], situational smoking abstinence self-efficacy [43], Proactive Coping Inventory [44,45]; and Patient Health Questionnaire-4 for anxiety and depression [46-48] (see Table 1).

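### Aim 3 picks mediators by P=.1 screens in the data used to estimate them, and turns post-randomisation candidates that miss the arm screen into covariates, which distorts the effects of weak-to-moderate mediators

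*Protocol article*

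**What the plan says.** The rules are in the Protocol article, section Aim 3: Mediational Analysis.

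- **Data.** "Using data from Aims 1 and 2, we will use multiple mediation models". No split sample, cross-fitting or correction for selection is described.
- **Candidates.** "Potential candidates for mediation include the number of helping conversations, change in personal network variables", and change in the patient-reported measures.
- **Screen.** To shorten the list, "we will first examine relationships between the intervention arm and the mediator, as well as the mediator and the outcome variable".
- **Entry as a mediator.** "Variables associated with both the intervention and abstinence", with a P "value of .1, will be included in this analysis as potential mediators".
- **Entry as a covariate.** "Variables associated with abstinence but not treatment arm at the 0.1 alpha level will be included as a covariate", and these are not explored further as mediators.

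Every candidate is post-randomisation. Helping conversations are counted during follow-up. For the networks, "Personal network measures will be obtained at two points, baseline and 12-month follow-up". For the survey scores, "the following patient-reported outcome measures are collected at baseline, 3, 6, 9, and 12 months post study enrollment". The stated targets are the direct effect of the intervention on abstinence and the indirect effects through these variables.

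**The concern.** There are two separate faults.

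First, the covariate rule treats failure to reach P<.1 against arm as if it meant no effect of arm. If the intervention does move the variable, and the variable is related to abstinence, it is a mediator. Entering it as a covariate blocks its path. That part of the randomised effect then appears in neither the direct nor the indirect estimate.

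Second, a candidate is kept because its estimated arm effect happened to be large enough, and the same estimate then goes into its indirect effect. For a weak mediator, the retained estimate is too large on average.

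At stake is the answer to Aim 3, one of the three stated aims. The article says the trial papers will follow the plans it describes, so the rules would be applied as written.

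**Working it through.** **1. Number evaluable.** Inputs from the section on power and sample size: control rate 0.25, difference 0.10, power 80%, dropout 30%, no continuity correction. Two-sided alpha 0.05 is assumed, since it is not stated.

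n per arm = [1.96·√(2·0.30·0.70) + 0.842·√(0.25·0.75 + 0.35·0.65)]² / 0.10² = 328.5, so 329 per arm and 658 in total. 658 / 0.70 = 940, which reproduces the plan's figure. No power is stated for the mediation analysis.

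**2. Power of the arm screen.** For a mediator in SD units, the standard error of the arm difference is √(2/329) = 0.0780. At alpha 0.1 the estimate must exceed 1.645 × 0.0780 = 0.128 SD. Power is approximately Φ(d/0.0780 − 1.645).

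**3. Overstatement among those retained.** If the outcome path nearly always passes, the mean arm effect given selection is that of a normal variable truncated at ±0.128:

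E = d + 0.0780·[φ(u) − φ(l)]/P, with u = (0.128 − d)/0.0780, l = (−0.128 − d)/0.0780, and P the probability of passing.

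For d = 0.10: u = 0.362, l = −2.93, P = 0.360, E = 0.180, which is 1.80 times the truth. The table sets the power beside a simulation with 658 participants and 4,000 runs. Its assumed outcome model is an abstinence probability rising 0.08 per SD of mediator, with a direct effect of 0.03.

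| True arm effect (SD) | Power of arm screen | True indirect effect | Mean if retained | Excess |
|---|---|---|---|---|
| 0.10 | 36% | 0.0080 | 0.0144 | 80% |
| 0.15 | 61% | 0.0120 | 0.0158 | 32% |
| 0.20 | 82% | 0.0160 | 0.0180 | 12% |
| 0.26 | 95% | 0.0208 | 0.0215 | 3% |

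Without screening, the means were 0.0079, 0.0120, 0.0160 and 0.0208, which is unbiased. A logistic version with log odds ratio 0.4 per SD gave 0.073 against 0.040 at 0.10 SD (83%) and 0.109 against 0.104 at 0.26 SD (5%).

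**4. One candidate turned into a covariate.** Assume a retained mediator with arm effect 0.26 SD, and a second true mediator that also feeds the first and fails the arm screen.

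| Arm effect on second mediator | Direct + indirect, rule applied | True total | Lost |
|---|---|---|---|
| 0.10 SD | 0.0301 + 0.0203 = 0.0504 | 0.0628 | 20% |
| 0.15 SD | 0.0287 + 0.0203 = 0.0490 | 0.0688 | 29% |

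These are means over the runs in which the rule applied: 65% of runs at 0.10 SD and 39% at 0.15 SD. With no arm effect on the second variable there was no material bias: indirect 0.0201 to 0.0206 against 0.0208, direct 0.0293 to 0.0306 against 0.0300.

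**5. Eight weak mediators (assumed log odds ratio 0.3 each).** At 0.10 SD the rule adds about 4.9 of the eight as covariates.

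- No separate direct effect: the arm log odds ratio falls from 0.204 to 0.142 (30%), and the risk difference from 4.3 to 2.8 points (35%).
- Direct log odds ratio of 0.25: the risk difference falls from 9.3 to 7.7 points (17%), and the log odds ratio by about 10%.
- At 0.26 SD, where few fail the screen: the log odds ratio moves from 0.548 to 0.541 (1%).

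**The case against.** **Scale.** The plan names d=0.26 as a good estimate of the minimum important difference for patient-reported outcomes. At that size both biases nearly vanish. This stands. The large percentages belong to mediators shifted by less than half as much, and no path size is given in the document. But nothing in the plan says the candidates will be shifted by 0.26 SD, and the rule acts on whatever size is true.

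**False positives.** A reader might infer that the screen multiplies false mediation claims. It does not. A mediator significant on both paths at .05 has almost always passed a .1 screen, so joint significance with no arm effect stays at about 4 to 5% with or without screening. What suffers is the interval read after selection: for a null mediator that passes, the 95% interval covers zero only about half the time.

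**Spurious entry.** Counting 1 count, 5 network and 8 survey candidates, 1 − 0.9^14 = 77% is the chance that at least one null candidate passes the arm screen, if independent. It is not the chance of entering the mediation model, which also needs association with abstinence. If all candidates were null on both paths, that chance is 1 − 0.99^14 = 13%.

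**Adjustment can be right.** A post-baseline variable that arm does not affect can be adjusted for safely and may be a needed mediator-outcome confounder. This stands, but P>.1 cannot tell such a variable from a weak mediator.

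**Reach.** The limitations section says the trial tests whether the intervention works overall, not which theoretical concept or mechanism works. That limits the weight of Aim 3 but does not withdraw its direct and indirect effects.

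**Conclusion.** The point holds for weak-to-moderate mediators. The article itself fixes both rules; they are not details left to an analysis plan.

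With about 658 evaluable, a true mediator shifted by 0.10 SD misses the arm screen about 64% of the time and, if related to abstinence, is adjusted away. Retained indirect effects are about 80% too large at 0.10 SD, 30% at 0.15, 12% at 0.20 and 3 to 5% at 0.26. With eight such mediators, the loss in the arm effect is about 15 to 30% at 0.10 SD (10% and 35% at the extremes of scale and scenario) and about 1% at 0.26. It is nil where arm truly does not affect the covariate.

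The overstatement depends on the assumed arm effect and on the outcome path nearly always passing. The loss depends also on the assumed outcome paths, the number of weak mediators and any direct effect.

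The document does not support the broader readings that the rules bias every result, that Aim 3 is worthless, or that the abstinence comparison in Aim 1 is affected. This is a change that should be made to a stated aim, not a threat to the trial's main result.

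**What to change.** - Drop the P=.1 arm and outcome screens as the rule for what counts as a mediator. Take the candidates already listed under Aim 3 as the pre-specified set.
- Estimate and report the indirect effect of every candidate whatever its path P values, with bootstrap intervals and a false-discovery-rate adjustment. Model correlated mediators jointly, since separately estimated indirect effects need not sum to the total.
- Delete the rule that makes a candidate a covariate because P>.1 against arm.
- In the main mediation analysis adjust for baseline covariates, including the mediator's baseline value. Address possible post-baseline mediator-outcome confounding by joint modelling or a sensitivity analysis.

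The cost is plan wording, more models, a longer results table and wider intervals. Some mediator-outcome confounding may remain and has to be faced in the sensitivity analysis. No new data are needed, and 12-month follow-up was still incomplete when the article was submitted.

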## Results

This trial was funded in 2021 and is currently ongoing. Initial study start-up was delayed when the first author, MM, moved to the University of Colorado. Recruitment began in December 2022, and we completed enrollment and randomization of 940 participants on September 15, 2025. As of August 31, 2025, when the paper was submitted, 337 participants (65%) had completed the study with the 12-month follow-up surveys.

## Discussion

### Principal Findings

We describe the protocol for a rigorous evaluation of a conceptually novel behavioral intervention for smoking relapse prevention with a study design and intervention addressing methodologic weaknesses and limited conceptual approaches to treatment in extant research [81].

Treatment approaches described in the literature have focused on skills-based interventions that encouraged identifying and resolving tempting situations, and minimal interventions using single sessions or written materials [81]. All behavioral interventions had abstainers apply skills to themselves [81]. Methodological limitations included small sample size, lack of clear separation between treatment and relapse prevention interventions, or insufficient detail to permit survival analyses [81]. Randomization of smokers who were already abstinent is recommended as the strongest design [81]. This ongoing pRCT addresses both methodological and treatment approach limitations of extant research, with a clear separation of cessation treatment from relapse prevention by randomly assigning smokers who have quit for at least 14 days. Helpers Stay Quit’s integration of behavioral theories and conceptual models is a conceptually novel approach to behavioral intervention, not previously studied.

Helpers Stay Quit’s “help others” presentation encourages abstainers to help other smokers to quit. Helpers Stay Quit integrates multiple behavioral theories into a novel intervention model that is presented as “help others.” Helpers Stay Quit teaches knowledge and skills to help others to quit tobacco, and thus could potentially increase an abstainer’s ability to influence their personal network in ways supportive of prolonged abstinence, for example, transmitting cessation behavior to smokers in the personal network [32,82]. This approach could potentially reinforce an abstainer’s identity as a nonsmoker and help shift the personal network social environment toward nonsmoking. Smoking-related identities and smoking behavior are reciprocally interrelated [41,83]. By offering helping conversations to others in their personal network, an abstainer publicly declares and reinforces a “quitter” or “non-smoker” social identity (vs smoker identity) within their personal network and to the abstainer themselves, creating a social expectation that favors abstinence and identification as a nonsmoker over time [84]. Engaging in prosocial helping behavior may be an alternate or additional proactive coping strategy for abstainers to deal with stressors potentially impacting relapse [85-87].

Research on the effect of social networks on smoking cessation and relapse among adults in the general population is limited. Most current studies of adult smoking and social networks focus on large online communities of tobacco users engaged in social media related to smoking and smoking cessation, for example, QuitNet [32,88-91], Become an EX [92,93], and Facebook pages with a smoking-cessation theme [94]. Much of the other research on smoking and social networks addresses adolescent or young adult smokers and smoking initiation [95] or pregnant and postpartum women [81]. Stone and colleagues [96] identified two different network approaches used in studies of personal networks and recovery from substance use, and by extension, smoking cessation: network predicting outcome and treatment predicting network change. The network predicting outcome studies are more prevalent and focus on the changes in the smokers’ personal network after cessation in a general population [90], during pregnancy [27], or among adults with serious mental illness [97]. Treatment-predicting network change studies are less common and include Helpers Stay Quit. Helpers Stay Quit is an intervention (“treatment”) intended to facilitate (“predict”) network change through helping conversations. There are several benefits to this approach. First, it allows participants to maintain their network members, which was identified as a factor in Nguyen and colleagues’ [27] study on why women did not stay quit after they gave birth. It also potentially reduces the participants’ contact with people who smoke by assisting their network members in quitting smoking, which was an important factor for those who stayed quit in Bray and colleagues’ study [90]. Finally, it leverages the valuable resource that people who quit smoking become for assisting other network members in quitting [97].

